## Abstract

**Introduction:**

The primary aim is to determine the factors associated with breast cancer-related lymphedema and to identify new associated factors for the recurrence of breast cancer and depression. The secondary objective is to investigate the incidence of breast cancer-related events (breast cancer-related lymphedema, recurrence of breast cancer, and depression). Finally, we want to explore and validate the complex relationship among multiple factors influencing breast cancer complications and breast cancer recurrence.

**Patients and methods:**

A cohort study of females with unilateral breast cancer will be conducted in West China Hospital between February 2023 and February 2026. Breast cancer survivors in the age range of 17–55 will be recruited before breast cancer surgery. We will recruit 1557 preoperative patients with a first invasive breast cancer diagnosis. Consenting breast cancer survivors will complete demographic information, clinicopathological factors, surgery information, baseline information, and a baseline depression questionnaire. Data will be collected at four stages: the perioperative stage, chemotherapy therapy stage, radiation therapy stage, and follow-up stage. Data including the incidence and correlation of breast cancer-related lymphedema, breast cancer recurrence, depression, and medical cost will be collected and computed through the four stages above. For every statistical analysis, the participants will be classified into two groups based on whether they develop secondary lymphedema. Incidence rates of breast cancer recurrence and depression will be calculated separately for groups. Multivariate logistic regression will be used to determine whether secondary lymphedema and other parameters can predict breast cancer recurrence.

**Discussion:**

Our prospective cohort study will contribute to establishing an early detection program for breast cancer-related lymphedema and recurrence of breast cancer, which are both associated with poor quality of life and reduced life expectancy. Our study can also provide new insights into the physical, economic, treatment-related and mental burdens of breast cancer survivors.

## Introduction

Breast cancer-related lymphedema (BCRL) is closely related to a high risk of cancer-related treatment, breast cancer recurrence, and disability [1]. In breast cancer patients, secondary lymphedema is a symptom cluster encompassing progressive upper-limb swelling, skin changes, limb numbness, pain and discomfort, restricted range of motion, and nonpitting edema [2]. These would decrease physical and mental function, increase disease burden and increase financial costs. It is a common complication in breast cancer patients [3–6]. Considering the establishment of a baseline of the upper limb and tracking changes, a screening cohort of secondary lymphedema may be the optimal solution to develop screening programs and evaluate the prevalence of breast cancer-related lymphedema in China.

Breast cancer recurrence (BCR) is a negative outcome in patients with breast cancer after either mastectomy or breast-conserving therapy (BCT) [7]. Breast cancer can recur locally, regionally, and/or at distant metastatic sites [8]. It is a hammer blow for breast cancer survivors [9]. It directly threatens breast cancer survivors’ life expectancy and decreases their quality of life. BCRL and BCR share risk factors such as higher BMI, pathological type, breast cancer location, tumor node metastasis(TNM) staging and comorbidities, and treatment-related factors (surgery, radiotherapy, and chemotherapy) [10]. Early detection helps implement personal and precise medical precautions for patients with secondary lymphedema (or breast cancer recurrence).

Up to 30% of breast cancer survivors have depressive symptoms [11]. Depressive affect includes emotional lability, irritability, and social withdrawal [12]. Depression is an emotional difficulty associated with an increased disease burden and treatment-related cost and a decreased ability to cope with breast cancer. Fear of cancer recurrence also directly affects mental health, especially anxiety and depression [13].

These three factors are significant risk factors for the disease burden of breast cancer. The disease burden of breast cancer is an area of concern [14]. The disease burden of breast cancer is a multidimensional construct comprising surgery, oncology-related treatment, drug costs and depression, and other elements destroying everyday life [15]. Therefore, a comprehensive screening plan that is feasible and responsive to reality may alleviate the symptom burden and reduce the economic burden of breast cancer patients.

Based on the retrospective data of the electronic medical record system in West China Hospital, we found a 3-year BCRL incidence rate of 17.57% after breast surgery or breast reconstruction in patients with breast cancer. The rate of BCR occurrence was 15.53% at three years. A previous study found that breast cancer recurrence may harm breast cancer-related lymphedema. However, whether BCRL is associated with the risk of breast cancer recurrence is uncertain. Moreover, there is a lack of evidence regarding the correlation between BCR, BCRL, and depressive symptoms, and there is also inadequate knowledge regarding the disease burden of breast cancer. This study aims to establish and evaluate whether a comprehensive screening plan for breast cancer may catch cancer early and improve the health situation and prognosis.

## Patients and methods

This study is a prospective cohort study of breast cancer survivors. This study aimed to investigate and evaluate the incidence and correlation of BCRL, BCR, and depression. The primary outcome measures include the incidence and correlation of BCRL and BCR within three years. Choice of the time frame because three years is a high-incidence period of BCRL and BCR. The secondary outcome is depression.

### Ethics approval and consent to participate

Our study period is between February 2023 and February 2026. The study was approved by the Ethics Committee of West China Hospital (Approval No. of ethics committee: 2019 Annual Review No. 664). Registration number: ChiCTR1900025534 (Name of the registry: Chinese Clinical Trial Registry (ChiCTR) http://www.chictr.org.cn/)

Our cohort study is in line with the international ethical principles and ethical processes of West China Hospital. All participants provided written informed consent. Breast cancer survivors will be informed that their identifying information will be confidential before participating in our cohort study. Fully informed consent will be obtained because the total duration of the study will span almost three years. Participants can withdraw at any time from the study. Fig 1 shows the participant flow.

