### Study sample

We will conduct a prospective cohort study of females with unilateral breast cancer in West China Hospital. We will recruit breast cancer patients between the ages of 18 and 55 years who will receive unilateral radical mastectomy or modified radical mastectomy, postoperative chemotherapy, and radiotherapy. Patients with breast cancer will be the first breast cancer diagnosed in West China Hospital, and the data on surgery and treatment will be extracted from the electronic medical record system. This cohort study will commence one week before breast cancer surgery and conclude after the three-year follow-up period.

Our study will need 1557 preoperative patients with a first-time invasive breast cancer diagnosis. Patients must meet the following criteria for inclusion.

Female subjects with ages older than 18 years and less than 55 years.Understand and sign the informed consent.Recruited in West China Hospital.First diagnosis of invasive breast cancer.Breast cancer patients will receive either radical or modified radical mastectomy.

There are four exclusion criteria; they are described briefly below.

Patients with bilateral breast cancerPatients had previously received neoadjuvant radiotherapy treatment before.Patients could not complete all the treatments and 3-year follow-up.There is significant asymmetry in the size of the upper extremities.The patients had cardiac dysfunction or renal and hepatic insufficiency.

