#### Last stage—follow-up stage

The follow-up stage is also the last stage of our cohort study. After finishing radiation and chemotherapy treatment, patients will be followed until 3 years after breast cancer surgery. Postoperative breast cancer patients are exposed to a chance of recurrence. The implementation of guideline-recommended follow-up plans for breast cancer patients is necessary. The patients in our study will be seen for follow-up visits once every three months [24]. Data will be collected at the time of the follow-up stage including BMI, upper limb volume measurement, assessment of tumor recurrence, and scale results of the Beck Depression Inventory II. Detailed cohort protocols in the four research stages are presented in Table 2.

**Table 2 pone.0285772.t002:** Detailed cohort protocols in four research stages.

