### Sample size calculation

Sample size will be estimated using the sample size estimation formula for prevalence studies. ($N=\frac{\mu_{\frac{\alpha }{2}}^{2}(1‐p)p}{d^{2}}$) [24, 25]. The formally required sample size calculation was based on the actual incidence of the primary outcomes in the electronic medical record system of West China Hospital. The maximum permissible error is 2%. Based on retrospective data from the electronic medical record system from 2017 to 2020 in West China Hospital, we found a 3-year BCRL incidence rate of 17.57% after breast surgery or breast reconstruction in patients with breast cancer. The rate of BCR occurrence was 15.53% at three years. Assuming a 10% dropout rate, at least 1557 participants should be recruited in our cohort study. We are trying to recruit more breast cancer patients, considering the longevity of the study.

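### The stated study period of February 2023 to February 2026 cannot hold staggered recruitment of 1557 women plus three years of follow-up after surgery for each

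*Protocol article*

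**What the plan says.** Two places in the protocol article give the same calendar. The section on ethics approval and consent says "Our study period is between February 2023 and February 2026" and adds that "the total duration of the study will span almost three years". The abstract says that the cohort study "will be conducted in West China Hospital between February 2023 and February 2026".

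The follow-up is fixed per woman. Under Study sample: "This cohort study will commence one week before breast cancer surgery and conclude after the three-year follow-up period". Under the last stage: "patients will be followed until 3 years after breast cancer surgery". Table 1 schedules a visit in the third year after surgery. The opening of the main Patients and methods section sets the time frame: "The primary outcome measures include the incidence and correlation of BCRL and BCR within three years".

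The Sample size calculation section uses three-year rates of 17.57% for breast cancer-related lymphedema (BCRL) and 15.53% for recurrence (BCR), with a maximum permissible error of 2%. It concludes: "Assuming a 10% dropout rate, at least 1557 participants should be recruited in our cohort study".

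The Statistical analyses section divides the number of women with an outcome by the number of participants in each stage. It compares groups by chi-square and models recurrence by logistic regression. The Missing data section keeps data from earlier stages for women lost later and rules out estimating missing values. Study sample also lists, among the exclusions, patients unable to complete treatment and the three-year follow-up.

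**The concern.** The calendar window and the follow-up required of one woman are practically the same length. Women having breast surgery at a single hospital enter one after another, so anyone operated on after the opening weeks would be cut off before her three-year visit.

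Both primary incidences are three-year quantities, and the sample size was chosen to estimate such a rate to within 2 points. The analysis named in the article takes no account of how long each woman was observed. Either the reported proportion mixes different lengths of follow-up and is no longer a three-year rate, or women without full follow-up are left out and few remain.

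**Working it through.** **The plan's own figure.** The article's formula is N = z² p(1 − p) / d². With p = 0.1757, d = 0.02 and z = 1.96 (two-sided 5% is an assumption, since no alpha is given):

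- N = 1.96² × 0.1757 × 0.8243 / 0.0004 = 1390.9, so 1391.
- With 10% dropout: 1391 / 0.90 = 1546, within 1% of the stated 1557.
- With p = 0.1553 the result is 1260, or 1400 after dropout, so the BCRL rate drives the target.

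The target therefore rests on about 1391 women evaluable for a three-year rate.

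**Time available against time needed.**

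- Available: 36 months. Counting from the first day of February 2023 to the last day of February 2026 gives about 37.
- Needed per woman: one week plus 36 months, about 36.25 months.
- Left for recruitment: 36 − 36.25 is below zero, and 37 − 36.25 = 0.75 months.

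With surgery dates spread evenly over A months, no one reaches 36 months after surgery in a 36-month window. In a 37-month window the share that can is 1/A: 33% for 3 months, 17% for 6, 8% for 12 and 4% for 24.

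**Effect on the crude rate.** The accrual period is not stated, so I vary it. Assumptions: uniform accrual over A months, closure at month 36, no other losses, and the article's rates P as the true three-year risks. With constant hazard h = −ln(1 − P)/36, the expected crude proportion is the mean of 1 − exp(−h(36 − u)) for u uniform on (0, A):

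crude = 1 − (1 − P)(e^(hA) − 1)/(hA)

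Example, BCRL with A = 12: h = 0.19322/36 = 0.005367 and hA = 0.06441. Then crude = 1 − 0.8243 × 0.06653/0.06441 = 14.9%.

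The alternative places 70% of the cumulative hazard in year 1 (also an assumption).

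| Accrual (months) | Mean follow-up (months) | BCRL, constant hazard | BCRL, early hazard | BCR, constant hazard | BCR, early hazard |
|---|---|---|---|---|---|
| 6 | 33 | 16.2% | 17.0% | 14.3% | 15.0% |
| 12 | 30 | 14.9% | 16.4% | 13.1% | 14.5% |
| 24 | 24 | 12.0% | 15.1% | 10.6% | 13.4% |
| True three-year rate | 36 | 17.57% | 17.57% | 15.53% | 15.53% |

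Under constant hazard, the shortfall first exceeds 2 points at 9 months of accrual for BCRL and 10 months for BCR. With early hazard it is about 1.2 points (BCRL) and 1.1 points (BCR) at 12 months, and about 2.4 and 2.2 points at 24 months.

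**The case against.** **The dates may describe recruitment only.** The follow-up sections promise three years, and the remark on total duration stands next to the consent statement, so it could describe one woman's participation. This is possible but the weaker reading: the abstract dates the conduct of the study, and the ethics section calls the same dates the study period. Even if recruitment was meant, the sentences need correcting, because no later end date appears. That correction would then remove the bias argument altogether.

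**The direction of the error is not fixed by the text.** This stands in part. Keeping earlier-stage data and counting all participants in a stage points to women staying in the denominator without later events, which lowers the rate. If the exclusion for incomplete three-year follow-up were applied to women cut off by the calendar, they would leave the denominator. The harm would then be few evaluable women, far below 1391, and not a low rate.

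**The size is uncertain.** This stands. A reader might infer that the bias exceeds the 2-point tolerance whatever the accrual. The figures do not support that: 6 months gives 1.3 points (BCRL) and 1.2 points (BCR) under constant hazard, and early events keep 12-month accrual inside 2 points.

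**The consent documents may be wrong as well.** A reader might infer this from the stated total duration. Those documents are not shown, so the point is limited to the article's own sentence.

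**Conclusion.** The contradiction stands with high confidence: a period of 36 to 37 months cannot contain staggered entry of 1557 women and 36 months of follow-up after surgery for each. As scheduled, the three-year primary outcome is unobservable for most of the cohort.

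The consequence is conditional. Under the natural reading of the crude calculation, the rates are too low. Under constant hazard, the shortfall for 6 to 24 months of accrual runs from 1.3 to 5.5 points for BCRL and from 1.2 to 4.9 points for BCR, and it is smaller if events cluster early. Under the exclusion reading, precision collapses instead. These sizes rest on assumed uniform accrual and assumed hazard shapes. The date conflict rests on neither.

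**What to change.** Reconcile the dates. State the recruitment window separately, set the end of the study at the last participant's surgery plus 36 months, and align the total duration given in the ethics section. With 12 months of accrual, for example, the window becomes 12 + 36 = 48 months. The cost is a later end date and the running of visits that the follow-up section already promises. No additional women are needed.

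If February 2026 cannot move:

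- Replace the crude proportions with Kaplan-Meier or Aalen-Johansen cumulative incidence, with administrative censoring at study close.
- Use a time-to-event model for recurrence in place of logistic regression.
- Restate the longest horizon that the follow-up supports, and its precision. With closure at month 36, the last entrant has 36 − A months of follow-up: 30, 24 or 12 months for accrual over 6, 12 or 24 months.

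This second route changes only the analysis text, but it gives up the full three-year horizon. On either route, say how the exclusion for incomplete three-year follow-up applies to women cut off by the calendar.

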**Fig 1 pone.0285772.g001:**
[figure not shown]
CONSORT 2010 flow diagram.

### Study sample

We will conduct a prospective cohort study of females with unilateral breast cancer in West China Hospital. We will recruit breast cancer patients between the ages of 18 and 55 years who will receive unilateral radical mastectomy or modified radical mastectomy, postoperative chemotherapy, and radiotherapy. Patients with breast cancer will be the first breast cancer diagnosed in West China Hospital, and the data on surgery and treatment will be extracted from the electronic medical record system. This cohort study will commence one week before breast cancer surgery and conclude after the three-year follow-up period.

Our study will need 1557 preoperative patients with a first-time invasive breast cancer diagnosis. Patients must meet the following criteria for inclusion.

Female subjects with ages older than 18 years and less than 55 years.Understand and sign the informed consent.Recruited in West China Hospital.First diagnosis of invasive breast cancer.Breast cancer patients will receive either radical or modified radical mastectomy.

There are four exclusion criteria; they are described briefly below.

Patients with bilateral breast cancerPatients had previously received neoadjuvant radiotherapy treatment before.Patients could not complete all the treatments and 3-year follow-up.There is significant asymmetry in the size of the upper extremities.The patients had cardiac dysfunction or renal and hepatic insufficiency.

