### Missing data

We will assess missing data and record the study stage and reasons for missing data. Data in the previous stage will be retained and calculated if patients are lost to follow-up at this stage of the study. Missing data will not be handled using estimation.

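### An exclusion for not completing treatment and 3-year follow-up cannot be judged before surgery; applied as written it selects on the outcome period and conflicts with the missing-data rule

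*Protocol article*

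**What the plan says.** In the protocol article, the Study sample section gives this exclusion criterion: "Patients could not complete all the treatments and 3-year follow-up". The same section fixes when the cohort starts: "This cohort study will commence one week before breast cancer surgery and conclude after the three-year follow-up period". The outcome period is set under Patients and methods: "The primary outcome measures include the incidence and correlation of BCRL and BCR within three years".

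Other sections treat non-completion as something that will happen to women already in the cohort:

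- Missing data: "Data in the previous stage will be retained and calculated if patients are lost to follow-up at this stage of the study".
- Ethics approval and consent to participate: women may withdraw whenever they wish.
- Limitations: some loss to follow-up is regarded as unavoidable.
- Statistical analyses: the incidence in each stage uses the participants in that stage as its denominator.
- Sample size calculation: "Assuming a 10% dropout rate, at least 1557 participants should be recruited in our cohort study".

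**The concern.** An entry criterion has to be decidable at entry. Whether a woman will finish chemotherapy, radiotherapy and three years of visits is not known before her operation. The criterion does not speak of expected inability or unwillingness at enrolment. Taken at its word, it can be applied only in retrospect, by deleting women who turned out not to complete.

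The period over which completion is judged is also the period over which the primary outcomes are counted. A woman who dies within three years cannot complete follow-up, and one too ill to finish treatment cannot complete treatment. The article itself links recurrence to shortened life and to most breast cancer deaths (Introduction; Discussion). Removing such women would therefore be expected to take out recurrences more than proportionately.

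Two results are at stake. One is the three-year recurrence incidence. The other is the comparison of recurrence between women with and without lymphedema, which could be distorted if completion depends on both conditions.

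**Working it through.** **1. The passages side by side.** The Study sample criterion, read literally, leaves only women who completed everything. The Missing data section keeps the earlier data of women who did not. Under the first rule the second has nobody to apply to. The withdrawal right and the expected loss to follow-up likewise presuppose non-completers inside the cohort. Two analysts could build different cohorts from this text, and nothing says which rule governs.

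**2. The plan's sample size.** Inputs from Sample size calculation: BCRL incidence 17.57%, permissible error 2 points, dropout 10%. Assumed, because no numeric level is given: two-sided 5%, z = 1.96.

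- N = 1.96² × 0.1757 × 0.8243 / 0.02² = 1391
- 1391 / 0.90 = 1546, against the stated 1557 (0.7% lower)
- Conversely, 1557 × 0.90 = 1401, slightly above 1391

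The stated figure is closely, though not exactly, reproduced. The allowance works whether the 10% are removed or merely incompletely observed, so it does not settle which reading is meant.

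**3. Illustrative bias in recurrence incidence.** Inputs: true three-year recurrence p = 0.1553 ("The rate of BCR occurrence was 15.53% at three years") and overall non-completion D = 0.10, borrowed from the dropout allowance. The article gives no completion rates by outcome, so f, the non-completion among women who recur, is an assumption shown as a range.

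- Non-completion among the others: g = (D − p·f) / (1 − p)
- Recurrence rate among completers: p(1 − f) / (1 − D)

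| f | g | f/g | Rate among completers | Bias (points) |
|---|---|---|---|---|
| 10% | 10.0% | 1.0 | 15.5% | 0 |
| 20% | 8.2% | 2.5 | 13.8% | −1.7 |
| 30% | 6.3% | 4.7 | 12.1% | −3.5 |
| 40% | 4.5% | 8.9 | 10.4% | −5.2 |

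For example, at f = 30%: 0.1553 × 0.70 / 0.90 = 0.1208.

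**4. Where the bias reaches 2 points.** Set p(1 − f)/(1 − D) = 0.1353. Then f = 1 − 0.1353 × 0.90 / 0.1553 = 0.216 and g = (0.10 − 0.1553 × 0.216) / 0.8447 = 0.079, a ratio of about 2.7.

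Fixing the ratio instead, at D = 10%, gives 14.3% for a ratio of 2, 13.3% for 3 and 11.9% for 5.

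**5. The association.** If the probability of completing were the product of a factor for lymphedema and a factor for recurrence, the odds ratio among completers would be unchanged. If the two act together in any other way, the odds ratio is distorted, in a direction that the article does not allow one to predict.

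**The case against.** The strongest reply is that the line sits in a list of entry criteria for preoperative patients and may simply mean women judged at baseline to be unable to complete. Neighbouring items use the past tense for baseline states, and such a criterion would be routine. No section describes a completers-only dataset, and the participant flow figure is not available to settle the matter. If the stage denominators and the Missing data rule govern, the bias calculated above does not arise in that form, and only ordinary loss to follow-up remains. This stands as a limit on how far one can say that harm will occur. It does not rescue the wording, which does not state a baseline judgement.

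The mechanism also has limits. A woman alive after recurrence can still attend visits. Table 1 starts the follow-up-stage visits at month 9, so many recurrences would come after adjuvant treatment has ended and could not interrupt it. Preferential loss of women who recur is thus a reasonable inference, not something the article states. The 2% in the sample size section is a sampling-precision term, used here only as a yardstick and not as a declared tolerance for bias.

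A reader might infer that the 10% dropout allowance is a further contradiction. It is not: inflating recruitment is what one does if non-completers will not be analysed, and it fits the other reading equally well. A reader might also infer that lymphedema and depression incidence must be understated too. The article gives no basis for a direction or size there, and none is claimed.

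**Conclusion.** The point holds as a defect in a stated eligibility rule. As written, the criterion depends on events after entry and within the primary outcome window, necessarily removes women who die within three years, and cannot be squared with retaining the data of women lost to follow-up. It is not established that the investigators will remove non-completers. The article supports only that the text permits this and that nothing rules it out.

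If the line is applied literally, recurrence is likely to be understated and the lymphedema–recurrence association may be distorted. The size is unknown. Under the assumed 10% overall non-completion it runs from no bias, when completion is unrelated to recurrence, to about 5 points when 40% of women who recur do not complete. It exceeds 2 points only when women who recur fail to complete at about 2.7 times the rate of the others.

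**What to change.** Delete the criterion, or reword it as something judged before surgery, such as known inability or unwillingness at enrolment to attend follow-up. Add one sentence on the analysis population: no enrolled woman is removed because she later stopped treatment, recurred, died or was lost, and her data are kept up to that point, as the Missing data section already provides. Treatment actually received can be recorded as a covariate.

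The cost is one eligibility line and one sentence. The 1557 already carries the dropout allowance, so no patients or procedures are added. The target population, women "who will receive unilateral radical mastectomy or modified radical mastectomy, postoperative chemotherapy, and radiotherapy", can stay as it is. The stage proportions, chi-square tests and logistic regression can also stay; a move to time-to-event analysis is not needed for this correction.
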